Assess the effectiveness of presumptive anti-relapse and transmission-blocking therapy with weekly low-dose primaquine (22.5 mg)^a^	Incidence of *P. vivax* recurrent infection and PCR-corrected *P. falciparum* recrudescence^a^ PCR-corrected absence of gametocytemia^a^
Evaluate the safety and tolerability of blood-stage antimalarials and weekly low-dose primaquine at 12 weeks versus 8 weeks in treated MMP and FSAT volunteers, respectively	Number of hemolytic events or other serious adverse events in participants over 13 years of age receiving primaquine
Assess level of antimalarial drug resistance at the selected study sites	Number of all-species malaria recurrence, established molecular markers of drug resistance, and clinical failure rates based on WHO criteria
Define the proportion of asymptomatic carriers of malaria in the study population	Cumulative incidence and incidence density of PCR-corrected parasitemia and submicroscopic parasitemia in each arm
Define the epidemiology of malaria infection in volunteers developing malaria	Cumulative incidence and incidence density of parasitemia
Compare the sensitivity and specificity of the currently recommended malaria rapid diagnostic test of choice in Cambodia with RT-PCR	Retrospective assessment of the proportion of asymptomatic carriers that would have been missed by each test and an estimate of the incremental cost-effectiveness of each test
Compare sensitivity and specificity of two currently available rapid diagnostic tests to detect moderate to severe G6PD deficiency using quantitative G6PD testing as the reference standard	Retrospective assessment of the proportion of persons with moderate to severe deficiency who would have been missed with each screening modality, and an estimate of the cost-effectiveness of each test
Describe population demographics to include the acceptability of FSAT, malaria prophylaxis, and use of vector control measures among participants, including willingness to participate in future malaria elimination campaigns	Descriptive analysis of participants’ responses to survey questions pre and post study regarding FSAT, malaria prophylaxis, and use of vector control measures

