Support host nation capabilities by improving the Royal Cambodian Armed Forces’ (RCAF’s) ability to diagnose, prevent, and treat malaria supported by robust data to achieve malaria elimination	A scalable military malaria elimination “unit of action” will be established at the provincial level, staffed by RCAF personnel trained during the course of the study

^a^Pilot study objective and endpoint added to assess operational feasibility given ongoing community concerns regarding these interventions. These endpoints are statistically underpowered and this data will be used to inform larger studies in the future

Lastly, an overarching aim of this operational study is to increase The Cambodian Military’s capability to diagnose, prevent, and treat malaria, and to understand the population’s willingness to participate in malaria elimination campaigns. To do so, a scalable military malaria elimination “unit of action” is being established at the provincial level, staffed by RCAF personnel who are trained during the course of this study. Regardless of the outcome, the study will provide critically important information to inform elimination policy in Cambodia and the GMS.

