### Cluster randomization, allocation, and blinding

Geographical areas were randomized prior to study start to a 1:1 allocation of MMP or FSAT using time- and region-blocked randomization to ensure that randomization is geographically distinct, and that malaria incidence is evenly distributed among groups given that high and low transmission areas exist. Volunteers meeting the enrollment criteria receive permethrin- or sham-treated (water-treated) uniforms according to their cluster’s assignment in single-blind fashion (volunteer blinded to assignment but not investigator). Entomology staff conducting uniform testing are also blinded to treatment. Diagnostic microscopists are blinded to each others’ readings and to study arm assignment. There is otherwise no blinding during the study.

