**Fig. 1 Fig1:**
[figure not shown]
Study flow diagram

**Table 2 Tab2:** Table of times and events for adults and children over 12 years of age

Event	Screen/enroll day 1	Day 3^3^	Day 30^7^	Day 60^7^	Day 90^7^	Day 120^7^	Day 150^7^	Day 180^7^	Malaria diagnosis/ recurrence^2^
a. Informed consent	X								
b. Medical history	X								
c. Physical exam	X								X
d. Brief clinical evaluation and vital signs^1^			X	X	X	X	X	X	X
e. Malaria RDT, DBS, smear and PCR genotyping^6^	2 mL		1.5	1.5	1.5	1.5	1.5	1.5	1.5 mL
i. CBC	1 mL	1 mL^3^							
k. Molecular resistance markers^2^									6 mL
l. G6PD RDT, fluorescent spot, quantitative testing	1.5 mL								
m. Gametocyte PCR	2.5 mL		2.5	2.5	2.5	2.5	2.5	2.5	2.5 mL
n. Urine pregnancy test (women of child-bearing age)	X		X	X					X
o. Malaria treatment^4,5^	X		X	X					X
Daily phlebotomy (mL)	7	1^3^	4	4	4	4	4	4	10
Cumulative phlebotomy (approximately mL)	7		11	15	19	23	27	31	41

^1^Brief clinical evaluation includes an interval medical history, vital signs and a directed physical exam as indicated

^2^Performed only for volunteers with smear-positive malaria. Those with PCR-positive malaria will be treated following national guidelines but will not have blood drawn for molecular markers of resistance

^3^To be drawn for G6PD-deficient volunteers only. All G6PD-deficient volunteers with > 10% of Hgb or HTC drop on D3 will have CBC on day 7

^4^Patients screening positive on microscopy and/or PCR for *P. falciparum* malaria in the FSAT arm will receive currently recommended blood-stage antimalarials under published national treatment guidelines as well as single, low-dose primaquine (15 mg). Volunteers with *P. vivax* will be treated with the currently recommended blood-stage agent (DHA-PIP), as well as primaquine – G6PD-normal volunteers will receive 15 mg daily for 14 days, while G6PD-deficient volunteer will receive 45 mg × 8 weeks. All volunteers in the MMP arm will receive a fixed-dose 3-day course of DHA-piperaquine at 0, 24 and 48 h starting on days 1, 30, and 60, and a weekly 22.5-mg dose of primaquine for 12 weeks. All therapy will be directly observed

^5^For all volunteers with recurrent malaria, rescue therapy will be with the recommended agent(s) per national guidelines

^6^May be repeated as medically indicated (e.g., if patient is malaria-positive or otherwise ill on enrollment). An additional 0.5 mL will be collected on the day of enrollment for baseline G6PD genotyping

^7^Time window of ± 7 days

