### Clinical procedures

Following documentation of informed consent/assent and determination of eligibility, a study physician completes an initial medical history and physical examination (Table 2). Volunteers aged 13 years and older have a rapid diagnostic test (RDT) for malaria, thick and thin blood films to estimate both sexual and asexual parasite densities, and malaria PCR diagnosis. Additional laboratory testing includes a complete blood count (CBC); an estimate of G6PD activity using quantitative testing to be compared with fluorescence and commercially available point-of-care testing; G6PD genotyping; real-time PCR to detect gametocytes; and analysis of molecular markers of resistance for those malaria positive at intake. Children aged 12 years and under have only rapid malaria diagnostic testing, malaria smears and PCR to detect submicroscopic parasitemia, with other testing deferred in children to reduce phlebotomy burden. Children less than 13 years of age are not tested for G6PD deficiency as they are not treated with PQ under this protocol. G6PD-deficient volunteers 13 years and older are counseled regarding the diagnosis, and have a repeat CBC on day 3 (± 1 day) following PQ treatment with repeat testing on day 7, if they have a greater than 10% drop in their hemoglobin or hematocrit, or at any time there are clinical signs of hemolysis.

All volunteers are followed monthly thereafter or at any time that they present with symptoms of suspected malaria, with a brief clinical evaluation and malaria diagnostics to include PCR assays for asexual and sexual parasites. Malaria-positive volunteers aged 13 years and older have additional tests for molecular markers of resistance. At these times, a swatch is taken from the volunteer’s uniform or clothing for repellency monitoring.

At the conclusion of the 180-day (− 2 to + 3 days) follow-up period, volunteers have blood drawn for malaria smears, RDTs, asexual blood-stage and gametocyte PCR diagnosis. If infection is noted at discharge, volunteers will continue to be followed until resolution of infection.

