Analysis of the effectiveness of MMP versus FSAT is the primary intervention (and outcome) of interest based on absolute risk reduction at 24 weeks. While the MMP arm reverts to standard-of-care (e.g., FSAT) after the 12-week intervention period, it would be unethical to not treat study participants who suffer new malaria infections during the follow-up period. This is intended to simulate a likely elimination program where an intervention is tried, and then the community defaults to standard of care while it is monitored afterward to determine effectiveness. While there is the potential for overlap between groups due to treatment during the follow-up period, the hypothesis is that the more intensive MMP intervention will reduce overall risk of disease further than the less intensive FSAT approach in the allotted study window. While we also wish to assess any additive effects of permethrin-treated clothing over pharmacological interventions in the treated clusters, the study is not powered based on permethrin treatment. In addition to estimation of additive effects, the intervention was performed to assess feasibility to effectively implement permethrin treatment and determine adherence to clothing wear.

It is anticipated and often argued that the large effort required to effectively achieve malaria elimination will preclude medical and safety monitoring. The feasibility of this approach will be assessed through analysis of diagnostic and adverse event data. If determined that elimination objectives could not be met without the intensity of medical monitoring to be employed here, it is possible that the study may conclude that approaches to malaria elimination studied here are not currently feasible. Technical, organizational and/or resource constraints may favor a more gradual approach as patient safety must always remain a paramount consideration. Regardless of outcomes, this initial study will serve as a pilot for scale-up efforts, and inform future operational approaches. Lastly, in an effort to optimize safety, due to phlebotomy limits for younger children, pediatric volunteers aged less than 13 years will not be screened for G6PD deficiency and will not receive PQ. While not expected based on known demographics of military dependents living along Cambodia’s borders, higher than anticipated pediatric enrollment could limit the study’s ability to discern potential benefits of the selected PQ dose.

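### Table 1 sets an effectiveness objective for weekly primaquine, but weekly primaquine is not randomised and, from age 13 up, cannot be separated from the MMP arm; the footnote discloses only a feasibility pilot with low power

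*Protocol article*

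**What the plan says.** **The objective.** Table 1 (Aim and objectives) includes the secondary objective "Assess the effectiveness of presumptive anti-relapse and transmission-blocking therapy with weekly low-dose primaquine (22.5 mg". Its endpoints are the incidence of P. vivax recurrence and of PCR-corrected P. falciparum recrudescence, and "PCR-corrected absence of gametocytemia". The row names no comparator.

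**What is randomised.** The section Cluster randomization, allocation, and blinding gives two factors, both assigned by cluster. For the drug strategy: "Geographical areas were randomized prior to study start to a 1:1 allocation of MMP or FSAT". For clothing: "Volunteers meeting the enrollment criteria receive permethrin- or sham-treated (water-treated) uniforms according to their cluster’s assignment in single-blind fashion". Primaquine is not a separate factor.

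**Who gets primaquine.** Under Treatment intervention, MMP volunteers aged 13 or over are assigned both monthly DHA-PIP and weekly primaquine; MMP children of 12 or less take DHA-PIP alone. In FSAT, primaquine follows a positive test. For P. falciparum, Table 2 footnote 4 says that such patients "will receive currently recommended blood-stage antimalarials under published national treatment guidelines as well as single, low-dose primaquine (15 mg" (closing bracket cut). For P. vivax it gives a 14-day daily course, or a weekly course in G6PD deficiency.

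**The caveats.** Footnote a to Table 1 labels the objective a pilot added to assess operational feasibility and then says: "These endpoints are statistically underpowered and this data will be used to inform larger studies in the future". The Limitations section adds that unexpectedly high pediatric enrolment could restrict the "ability to discern potential benefits of the selected PQ dose".

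**The concern.** The objective asks what weekly primaquine achieves. The design can show what the MMP package achieves against FSAT. Fewer vivax recurrences or less gametocytemia in MMP could come from three monthly rounds of DHA-PIP given to everyone, from weekly primaquine, or from both.

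Footnote a points the reader to sample size as the weakness and to larger studies as the next step. If the weakness is instead that two drugs are always given together, enlarging the same design does not help, and a package effect could be carried forward as a primaquine effect. This matters because the Background describes severe hemolysis as a risk of primaquine in G6PD deficiency. A benefit wrongly assigned to the drug would distort the weighing of that risk.

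**Working it through.** The protocol gives no figure for this objective, so there is none to reproduce. The check is whether the assigned treatments allow a primaquine effect to be estimated.

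**Inputs.** From Study design and Treatment intervention, assigned treatment depends on arm and age only. Code each of four cells as (intercept, age 13 or over, monthly DHA-PIP, weekly primaquine):

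| Cell | Intercept | Age ≥13 | Monthly DHA-PIP | Weekly primaquine |
|---|---|---|---|---|
| MMP, 13 or over | 1 | 1 | 1 | 1 |
| MMP, 12 or less | 1 | 0 | 1 | 0 |
| FSAT, 13 or over | 1 | 1 | 0 | 0 |
| FSAT, 12 or less | 1 | 0 | 0 | 0 |

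Monthly DHA-PIP is the same column as the MMP arm.

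**Step 1: age 13 or over.** Keep rows 1 and 3 and the columns intercept, DHA-PIP and primaquine: (1, 1, 1) and (1, 0, 0). Three columns, rank 2. If d is the DHA-PIP effect and q the primaquine effect, the arm difference equals d + q: one equation, two unknowns. Adding people or clusters makes d + q more precise and leaves the rank at 2. The clothing factor does not help, because primaquine does not vary within an arm in this age group, whichever clothing a cluster receives.

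**Step 2: all ages, additive model.** Four rows, four columns, rank 4. A primaquine term can be fitted, and it equals

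q = (MMP ≥13 − FSAT ≥13) − (MMP ≤12 − FSAT ≤12).

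This is the arm-by-age interaction. Adding an explicit arm-by-age column gives five columns, still rank 4. So q can be read as primaquine only if MMP without primaquine, relative to FSAT, has the same effect in children as in adults. Age decides who gets primaquine, and the protocol neither states nor supports that assumption.

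**Step 3: what FSAT contributes.** FSAT is not primaquine-free. Test-positive FSAT patients receive their own primaquine regimens, so even a clean contrast would compare weekly presumptive primaquine with test-triggered primaquine. The Limitations section also says that MMP reverts to standard of care after the 12-week intervention, so later follow-up narrows the difference between the arms.

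**Step 4: footnote a, row by row.** The footnote covers both the clothing objective and the primaquine objective. Clothing has its own randomised sham comparator, so low power is a fair description of its main weakness. Primaquine has no such comparator, so the same sentence omits its main weakness.

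**The case against.** **It is a declared feasibility pilot.** Footnote a says so, and Statistical methods calls the secondary endpoints pilot endpoints. This stands and limits the weight of the point. It does not remove it: the row is worded as effectiveness and its endpoints are parasitological, not measures of feasibility.

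**No primaquine effect size is planned.** The row names no comparator, and Statistical methods compares incidence between the prophylaxis and FSAT groups, that is, between strategies. This also stands. The misattribution is a risk created by the wording, not an analysis that the protocol commits to.

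**Primaquine in FSAT is a natural comparator.** The objective concerns presumptive therapy, so test-triggered primaquine is a reasonable control and no defect in itself. Agreed; the obstacle is that DHA-PIP changes at the same time.

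**Primaquine has a distinct action.** The Discussion says that only primaquine has been shown to treat mature gametocytes. But gametocytemia also falls if DHA-PIP clears or prevents the blood-stage infections behind it, so an arm difference remains unattributable.

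**The analysis plan could deal with it.** An analysis plan can define populations and models. It cannot create a contrast that the assignment lacks.

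**Stronger readings that the protocol does not support.**
- A reader might infer that DHA-PIP is never given without primaquine, or that nothing can be fitted at any age. MMP children of 12 or less take DHA-PIP alone, and the all-ages additive model has full rank. The contrast is weak and non-randomised, but it exists.
- A reader might infer that children have no gametocyte PCR, because Clinical procedures says: "Children aged 12 years and under have only rapid malaria diagnostic testing, malaria smears and PCR to detect submicroscopic parasitemia". That sentence stands in the paragraph on enrolment testing. The next paragraph gives all volunteers monthly PCR for asexual and sexual stages, the day-180 paragraph sets no age limit, and Table 2 covers only those over 12. The section is inconsistent on children, so absence is not established and the argument here does not use it.
- A reader might infer that the Limitations sentence on pediatric enrolment is wrong. It is true as written, since more children means fewer primaquine recipients, and it does not claim to list every obstacle.

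**Conclusion.** The point holds for the stated objective. In volunteers aged 13 or over, weekly primaquine is completely aliased with the MMP arm (rank 2 for three columns), so any arm difference in these endpoints belongs to the package and cannot be divided between DHA-PIP and primaquine at any sample size. Across all ages, a primaquine term rests entirely on assuming no arm-by-age interaction apart from primaquine. Footnote a discloses low power and pilot status but not this confounding.

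The conclusion assumes only that treatment is assigned as Study design and Treatment intervention describe. Its practical weight is modest: one declared pilot secondary objective is affected, and the primary objective already treats DHA-PIP plus primaquine as a combination.

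**What to change.** 1. In Table 1, restate this secondary objective and its endpoints as the effect of the combined MMP regimen (DHA-PIP plus weekly primaquine) versus FSAT on P. vivax recurrence, P. falciparum recrudescence and gametocytemia.
2. In footnote a, add that primaquine's separate contribution cannot be estimated because it is confounded with DHA-PIP, and that this is not merely a matter of power.
3. Report these endpoints separately for those aged 13 or over and for children of 12 or less, so that the group assigned primaquine is visible.

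The Limitations sentence on pediatric enrolment can stay. The cost is the wording of one objective, one footnote and an extra split in the tables; no treatment or data collection changes. The downside is a less ambitious claim.

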## Methods/design

### Study design

We are conducting a two-arm, cluster-randomized, open-label controlled trial of MMP with t3-day DHA-PIP and weekly PQ compared to focused screening and treating (FSAT) following current national treatment guidelines. Participants in the MMP arm receive a monthly 3-day course of fixed-combination tablet containing 40 mg of dihydroartemisinin and 320 mg of piperaquine phosphate for three consecutive months. Those aged 13 years and older receive low-dose weekly PQ (22.5 mg) therapy to prevent malaria transmission for 12 weeks. Participants in the FSAT arm are screened with highly sensitive polymerase chain reaction (PCR) methods, and all those testing positive for malaria receive therapy with first-line antimalarials following current national treatment guidelines. At the time of protocol development, artesunate-mefloquine combination therapy is the first-line treatment for *P. falciparum* in provinces with known antimalarial resistance, with a single, low dose of PQ (15 mg) to prevent malaria transmission. For participants in the FSAT arm with *Plasmodium vivax* malaria, the recommended treatment for asexual parasitemia is DHA-PIP. All patients with *P. vivax* in the FSAT arm receive treatment with 15 mg of PQ daily for 14 days if G6PD normal, or 45 mg weekly if G6PD deficient.

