### Study site and population

The study takes place at multiple military encampments in malaria-endemic areas in border areas authorized by the Ministry of National Defense. Sites were chosen based on current malaria incidence estimates by the RCAF health services in consultation with the National Center for Parasitology, Entomology, and Malaria Control (CNM) in Cambodia and the Armed Forces Research Institute of Medical Sciences (AFRIMS). For reasons of operational security, locations or other descriptors will not be further described here. All sites will be evaluated as simultaneously as feasibly possible.

Military volunteers aged 18–65 years of age and their dependents of ≥ 2 years of age, eligible for care at an RCAF facility, or otherwise eligible Cambodian civilians at risk for contracting malaria who live within close proximity, are enrolled if they meet the following criteria: are able to give informed consent/assent; reside in the selected study areas; are available for monthly follow-up for 6 months; agree not to seek outside medical care for febrile illness unless referred by study team; and are authorized by respective military unit commanders to participate in the study if on active duty. Volunteers who have known allergy or other contraindication to study medication; are pregnant, lactating or are women of childbearing age who do not agree to use an acceptable form of contraception during the study; or are judged by the investigator to be otherwise unsuitable for study participation are excluded from the study.

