### Treatment intervention

Volunteers randomized to MMP arm aged 13 years and older receive a monthly 3-day treatment course of (DHA-PIP; 360/2880 mg) for 3 months. They will also receive a weekly dose of 22.5 mg of PQ for 12 weeks. Children of 12 years of age or less will receive only a monthly 3-day weight-based treatment dose of DP for 3 months without PQ treatment. In the MMP arm, symptomatic patients or microscopy-confirmed parasitemia in the first 3 months are considered a failure of prophylaxis and treatment is given according to the national treatment guidelines. If the volunteer has parasitemia detectable by PCR only and is symptom free at monthly follow-up, the study treatment with monthly DHA-PIP is continued for 3 months as outlined for the MMP arm. To reduce phlebotomy requirements for G6PD testing and potential hemolytic risk in children, PQ is not be administered to those less than 13 years old.

Volunteers randomized to the focused screening and treatment (FSAT) arm are treated according to current national malaria treatment guidelines if they test positive for malaria based on blood smear and/or real-time PCR results during monthly follow-up. In the FSAT arm, all volunteers with parasitemia detectable with PCR receive antimalarial treatment, even if they are symptom- free.

At the time of protocol development, national treatment guidelines for areas of known piperaquine resistance, to include the designated study regions, recommended a 3-day course of artesunate and mefloquine (A + M) and a single 15-mg dose of PQ for acute *P. falciparum*, or DP for blood-stage *P. vivax* infection. Elimination interventions are carried out monthly during the first 3 months after enrollment, and then followed by 3 months of additional malaria assessment by smear and PCR diagnosis with malaria treatment as necessary following current national treatment guidelines (Fig. 1, Table 2, Fig. 2). Those febrile but negative for malaria are referred for evaluation and treatment of alternative diagnoses.

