### Primaquine and transmission-blocking therapies

While considered an essential component for malaria elimination [45–47], the safety of PQ must be given careful consideration given the risk of hemolysis in G6PD-deficient individuals, who may be at even more risk in a large-scale elimination campaign that does not allow for close, individual follow-up [48]. Grimmond et al. demonstrated safe use of 22.5 mg of PQ weekly in combination with chloroquine for 8 weeks to prevent *P. vivax* relapse in a cohort of Southeast Asian refugees in Australia in 1984 [49]. This work and other more recent dose-ranging studies informed selection of PQ dosing in the present study [45, 49]. Risks of PQ administration have been further mitigated in the study with extensive G6PD screening using three modalities (rapid test, qualitative, and quantitative testing) on individuals aged 13 years and over who will receive PQ. Data generated by the study will be highly informative for defining the minimum diagnostic G6PD-deficiency screening requirements to deliver a safe and effective elimination program nationally.

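### The Table 1 safety endpoint counts events only in primaquine recipients over 13, which is narrower than its own objective and than the safety population in Statistical methods

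*Protocol article*

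**What the plan says.** The relevant row of Table 1 (protocol article, Aim and objectives) has this objective: "Evaluate the safety and tolerability of blood-stage antimalarials and weekly low-dose primaquine at 12 weeks versus 8 weeks in treated MMP and FSAT volunteers". It sets no age limit and names blood-stage drugs alongside primaquine. The endpoint in the same row is "Number of hemolytic events or other serious adverse events in participants over 13 years of age receiving primaquine".

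Other sections say who is enrolled and what they receive:

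- Study site and population admits military volunteers and "their dependents of ≥ 2 years of age".
- Study design, for the MMP arm: "Those aged 13 years and older receive low-dose weekly PQ (22.5 mg) therapy". The Discussion section on primaquine repeats the threshold when it describes G6PD screening "on individuals aged 13 years and over who will receive PQ".
- Treatment intervention, for the MMP arm: "Children of 12 years of age or less will receive only a monthly 3-day weight-based treatment dose of DP for 3 months without PQ treatment". Clinical procedures confirms that no child under 13 is given primaquine under this protocol.

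Statistical methods describes the safety analysis in two sentences. One takes all volunteers with at least one follow-up assessment. The other builds the safety database from randomized volunteers who had at least one dose of study drug. Neither has an age or primaquine condition.

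**The concern.** The endpoint carries two conditions, an age limit and receipt of primaquine, that its objective does not have. Both exclude children aged 2–12. By design these children are the one group given a blood-stage drug without primaquine, so they are where harm from the blood-stage drug could be seen apart from primaquine. The Discussion names QT prolongation as a known effect of piperaquine, and the abstract announces a comparison of the safety of the interventions as a whole. In children, the MMP intervention is DHA-PIP alone, given whether or not they are infected. An endpoint that cannot register a serious adverse event in such a child leaves part of its objective unmeasured.

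The age wording raises a second, smaller issue. Read in completed years, *over 13* leaves out the 13-year-olds, who are the youngest people given primaquine. An analyst programming Table 1 as written would drop them.

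**Working it through.** The point concerns who is counted, so the main check sets the passages side by side. The article gives no figure to reproduce.

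**Step 1. Apply each rule to each treated group.** Inputs are the Table 1 endpoint, the dosing rules in Study design, Treatment intervention and Clinical procedures, and the safety population in Statistical methods. The last column uses the rule of at least one dose of study drug.

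| Treated group | Drugs received | Counted by the Table 1 endpoint | In the safety set |
|---|---|---|---|
| MMP, age 2–12 | DHA-PIP, 3 courses, no primaquine | No | Yes |
| MMP, age 13 | DHA-PIP, 3 courses, and primaquine | No, if read literally | Yes |
| MMP, age 14 and older | DHA-PIP, 3 courses, and primaquine | Yes | Yes |
| FSAT, age 2–12, test positive | Blood-stage drug, no primaquine | No | Yes |
| FSAT, age 13, given primaquine | Blood-stage drug and primaquine | No, if read literally | Yes |
| FSAT, age 14 and older, given primaquine | Blood-stage drug and primaquine | Yes | Yes |

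All six groups fall within the objective and the safety set, and the endpoint counts two of them. Children aged 2–12 fail both of its conditions. The 13-year-olds fail only the age condition.

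**Step 2. Check whether the safety population repairs the endpoint.** It does not. Statistical methods defines whose data enter the safety analysis, while Table 1 defines which events the named endpoint counts. A child can be in the first and still add nothing to the second.

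**Step 3. Illustrate the size in the MMP arm.** Sample size rationale proposes 8 clusters of 80–140 volunteers. Allocation is 1:1, so MMP has 8 / 2 = 4 clusters.

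- MMP volunteers: 4 × 80 = 320 to 4 × 140 = 560.
- Share aged 2–12: not given. Assume 5–30%.
- Children outside the endpoint: 0.05 × 320 = 16 to 0.30 × 560 = 168.
- DHA-PIP courses outside it, at 3 per child: 16 × 3 = 48 to 168 × 3 = 504.

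The width of this range comes mostly from the assumed share. The number of FSAT children treated also depends on how many test positive, so no figure is offered for them. The mismatch in Step 1 depends on none of these numbers.

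**The case against.** The strongest reply is that nobody is lost. Statistical methods puts every dosed volunteer into the safety database without an age limit, and the Limitations section plans to use adverse event data. This stands, and it limits the point. A reader might infer from Table 1 that children and 13-year-olds escape safety evaluation altogether, but the article does not support that.

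Second, the 12 and 8 weeks in the objective describe primaquine, so the objective could mean the combined regimen, which would fit an endpoint in primaquine recipients. That reading is possible. Yet the objective lists blood-stage antimalarials separately and covers treated volunteers without an age limit. For a child, the MMP regimen contains no primaquine.

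Third, a reader might infer that the endpoint says nothing about blood-stage drugs. That goes too far. In MMP everyone aged 13 and older is due both drugs, and both FSAT regimens described include primaquine. Age boundary aside, the endpoint therefore captures serious adverse events in nearly all participants of that age given a blood-stage drug.

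Fourth, a reader might infer that the endpoint favours MMP, because MMP children are dosed without a positive test. The direction is not established. At the ages it does count, the endpoint is a raw number covering all MMP volunteers but only treated FSAT volunteers, which loads events onto MMP.

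Fifth, *over 13* is probably loose wording. Table 2 is headed for those over 12, and nothing suggests an intent to exclude 13-year-olds. I accept this, but the text still needs correcting.

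Finally, this is a condensed article, these are pilot endpoints, and detailed tabulation belongs in the full protocol or analysis plan. That would answer a complaint about missing detail. It does not answer a stated endpoint that disagrees with its own objective.

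**Conclusion.** The point holds as an inconsistency. The Table 1 safety endpoint is narrower than the objective beside it and than the safety population in Statistical methods. Children aged 2–12 given a blood-stage drug without primaquine cannot contribute an event to it, and its age limit does not match the primaquine threshold of 13 and older. The child exclusion is the substantive part. The age boundary affects a single year of age.

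The loss is confined to this endpoint count, and no direction of bias between arms is shown. The size is unknown because no age distribution is given. The range of 16–168 MMP children rests on the assumed 5–30% share, and Limitations says high pediatric enrollment is not expected, which argues against the upper end. The correction is worth making because it is cheap and the conflict lies in stated rules.

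**What to change.** Reconcile the Table 1 row with its objective and with Statistical methods by stating the endpoint in two parts:

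1. Hemolytic events in all primaquine recipients aged 13 years and older.
2. Serious adverse events in all volunteers who receive at least one dose of any study antimalarial, by arm and by age group (2–12, 13 and older), with the number exposed in each cell.

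The number exposed is needed because MMP doses everyone and FSAT doses only those who test positive, so raw counts cannot be compared between arms.

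The cost is one line in Table 1 and one more tabulation. Clinical procedures already plans monthly clinical evaluation of all volunteers, children included, so no visit, sample or treatment rule changes.
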